#### Qualitative evaluation

We will analyse parent and staff interview transcripts, identify and code themes using a Grounded Theory Approach.^22^ We will analyse results by theme and produce a summary report of how parents and staff interact on the neonatal unit, how information exchange takes place, how parents and staff feel about it and would like it to happen (precommunication and postcommunication tool usage). We will also produce a summary report of parents’ and staff impressions of the communication tool.

## Discussion

This study will evaluate the impact of a parent co-designed intervention to improve communication in neonatal care. The strengths of this study include the active involvement of parents throughout, from conception and design through to dissemination, and that parents with infants receiving neonatal care are prospectively co-designing the intervention. A further strength is that the intervention uses routinely recorded NHS neonatal infant data, without incurring any extra work to staff. In contrast to previous studies, we are using a parent satisfaction questionnaire validated with parents of babies receiving NHS neonatal care to evaluate our intervention. These parent survey data will also be used to further develop and improve the intervention by analysing parent free-text feedback and conducting PDSA improvement cycles. Finally, because parent satisfaction is not a static measure, but can change over time (even in the absence of any interventions), we are comparing outcome measures post intervention to routinely recorded longitudinal baseline measures, rather than single preintervention and postintervention measures. Limitations of our study include involvement only of parents that can speak and understand written English. This is because parents need to be involved in the co-design: our self-administered survey is only available in English and this process cannot easily be facilitated using interpreters. Another limitation is recruitment, which will be done using a non-randomised design and therefore is susceptible to bias. Randomisation of an intervention such as that being developed and evaluated in this study is inherently difficult to blind and has a high risk of contamination; parents in neonatal care regularly converse and exchange ideas. In order to avoid specific parent characteristics influencing the study’s outcomes, we will measure and correct for parent demographic details. We will also describe any other relevant parent-centred co-interventions taking place during our study period. Finally, as with any survey-based study we may have significant drop off. Survey responses are subjective and can be influenced by many factors, including parental anxiety, depressive symptoms, severity and changes in infants’ condition, which we are not measuring, as our study is a small-scale pilot. A cluster RCT may be the optimal methodological approach to definitively evaluate an intervention such as this; our study will inform such a future cluster RCT to further evaluate the impact of sharing routinely recorded infant information in neonatal care.

On completion of this study we will have also identified the final template of EPR data items that parents would like to receive on a daily basis in neonatal care. The incorporation of these findings into a digital medium, such as a mobile phone application and/or website, would allow for better efficiency and wider generalisability of the study findings.

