The aim of this study is to use existing, routinely recorded data, from existing neonatal electronic patient record systems (EPR) to implement, further co-develop and evaluate a neonatal communication tool with parents. In the UK a defined set of data items are extracted from neonatal EPR systems to form the National Neonatal Research Database (NNRD).^14^ This holds information on all babies admitted for NHS neonatal care and is used for audit, benchmarking and research, but is currently not routinely shared with parents. The completeness of data in the NNRD is high^14^ but has the potential to further improve. There is a lack of evidence for interventions to improve the completeness of routinely collected data in neonatal care and more widely.

We will evaluate the impact of sharing routinely recorded infant information with parents, on parent satisfaction with ‘communication of clinical information and involvement in care’ using a validated questionnaire, and on the completeness of NNRD data extracted from neonatal EPR systems. We hypothesise that sharing individualised, daily EPR data with parents will lead to higher reported parent satisfaction and data completeness.

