### Communication tool

We previously identified the information parents report as important when their baby is on a neonatal unit through qualitative work with ex-neonatal parents. This information was matched to the routinely recorded neonatal daily EPR data items and we developed parent-friendly explanations of these EPR data items with parents. We co-designed a communication tool template for parents called ‘*My Baby’s Summary Report*’; this comprised a printed sheet of paper including individualised, daily infant updates for parents derived from EPR data, in parent-centred language.

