### Design

A prospective before-and-after study employing mixed methods. The intervention (the communication tool) will be implemented in stages across the three intensity unit areas of the Chelsea and Westminster hospital neonatal intensive care unit (from low to high) over an 8-week period; a 2-week proof of concept phase will precede a 6-week roll-out phase (figure 1). An individualised *‘My Baby’s Summary Report’* will be administered to recruited parents in a sealed envelope every weekday. Quality improvement methodologies, including Plan-Do-Study-Act (PDSA) cycles^18–20^ and run-charts^21^ will be used to implement and further improve the communication tool. The content and the exact timing of the implementation in relation to the study will be fully described to avoid other concurrent parent-centred interventions influencing our study results.

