#### Secondary outcomes

Parent–staff interactions: Assessed by the PEC survey.Staff workload: Staff members will be asked to complete a three-question Staff Survey:

In the last 24 hours, have you updated parents during a ward round? Y/NIn the last 24 hours, how many times have you spoken to parents face-to-face about their baby (outside ward round times)?In the last 24 hours, how many times have you spoken to parents over the phone?

EPR data completeness and accuracy (expressed in %): The lead researcher will compare EPR-recorded data to handwritten clinical documentation to produce a daily measure of data completeness.Qualitative evaluations: The lead researcher will conduct one-on-one in-depth interviews with parents (30 min) and staff members (10 min). Interviews will explore the parent experience of receiving information updates in neonatal care and feeling involved in their baby’s care (see online supplementary file 1). For staff, interviews will explore their experience of giving parents information updates and perceptions of how updating parents affects their workload (see online supplementary file 2). Interviews will be recorded and anonymously transcribed.

10.1136/bmjpo-2019-000515.supp1Supplementary data

10.1136/bmjpo-2019-000515.supp2Supplementary data

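### Unit area, a known marker of infant severity that changes with calendar time by design, is not named for adjustment, and the small-pilot reason does not justify leaving it out

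*Protocol article*

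**What the plan says.** The primary outcome is parent satisfaction from the PEC survey (Primary outcome). The Discussion names several influences on survey answers, among them parental anxiety, depressive symptoms, and how sick the infant is and how that changes, and says of them "which we are not measuring, as our study is a small-scale pilot". Against differences between parents it offers one correction: "we will measure and correct for parent demographic details". The form behind that correction, described under Parents, covers the parent's age, gender and ethnic group, and also the infant's gestational age and length of stay.

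The intervention is brought in by area of the unit, in the words of the Design section "from low to high) over an 8-week period". The Parents section gives SCBU 4 weeks and describes its babies as stable. HDU parents are recruited in addition for 2 weeks, and ICU parents for the final 2. The Stage 2 heading gives 2 weeks to each area.

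Under Analysis, run charts show change over time, and a partially paired comparison sets the intervention period against a 6-week service-evaluation baseline. The area mix of the baseline surveys is not given.

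**The concern.** The authors name a factor that moves their primary outcome and give study size as the reason for not measuring it. Size is a fair reason for not adding anxiety or depression instruments, which need new answers from parents. It is not a reason for leaving out the unit area, a coarse marker of how sick the baby is that recruitment itself supplies.

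The staged roll-out makes this matter. Early intervention surveys come from parents of stable babies, and later ones increasingly or wholly from parents of sicker babies. A run chart would show this shift as a change in satisfaction even if the tool did nothing. The before-and-after difference would also carry it wherever the baseline respondents have a different area mix. Because the pilot is meant to inform a cluster RCT, a distorted estimate would be carried forward.

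**Working it through.** The article gives no effect size, SD, baseline number or baseline area mix, so there is no stated figure to reproduce. What follows shows scale only.

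**From the document:** the order SCBU, HDU, ICU; three 2-week roll-out blocks; at most 90 parents in Stage 2.

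**Assumed:** satisfaction gaps between areas, area shares, and lower scores among ICU parents.

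**1. Simple bias.** Bias = satisfaction difference (SD) × difference in high-severity share between periods.
- Low end: 0.3 × 0.10 = 0.03 SD
- High end: 0.7 × 0.30 = 0.21 SD

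As a yardstick, 90 independent parents in each period would give SE = √(2/90) = 0.149 SD. The bias is then 0.03/0.149 = 0.2 to 0.21/0.149 = 1.4 standard errors. This is only a yardstick: 90 is a recruitment cap, the baseline number is unknown, and the data are partially paired.

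**2. Bias by roll-out block.** Let ICU parents score g SD below SCBU parents, with HDU halfway and no tool effect. The text allows two readings of recruitment.

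*Areas added cumulatively, in equal shares:*
- Block means: 0; ½ × (−g/2) = −g/4; (0 − g/2 − g)/3 = −g/2
- Drift from first to last block: −g/2
- Period mean: (0 − g/4 − g/2)/3 = −g/4

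*Areas strictly in sequence:*
- Block means: 0, −g/2, −g
- Drift: −g
- Period mean: −g/2

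A baseline drawn equally from the three areas has mean −g/2. A baseline drawn only from SCBU has mean 0. Bias is the period mean minus the baseline mean.

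| g (SD) | Drift, cumulative | Drift, sequential | Bias, cumulative, equal baseline | Bias, sequential, equal baseline | Bias, cumulative, SCBU-only baseline |
|---|---|---|---|---|---|
| 0.1 | −0.05 | −0.10 | +0.025 | 0 | −0.025 |
| 0.3 | −0.15 | −0.30 | +0.075 | 0 | −0.075 |
| 0.5 | −0.25 | −0.50 | +0.125 | 0 | −0.125 |
| 0.7 | −0.35 | −0.70 | +0.175 | 0 | −0.175 |

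The run-chart trend is distorted under both readings. The period comparison may be biased up, down or not at all, depending on the baseline mix, which the document does not give.

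**The case against.** The strongest reply is that this is a pilot which discloses the limitation, already collects two infant variables related to severity, and may leave its covariate list to a fuller document. Much of that stands. Gestational age and length of stay are on the form, so it would be wrong to say that no infant factor is available for correction. The before-and-after bias may be zero. Pairing removes stable differences between the parents who are paired, though not a change in the baby's condition or a move between areas. Disclosure, however, does not remove a bias that is cheap to avoid. And the decision not to measure is stated, with a reason, in this document; it is not a detail left for later.

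A reader might infer more: that severity is already captured for everyone in both periods. The reports are "individualised, daily infant updates for parents derived from EPR data", the lead researcher compares the EPR with clinical notes daily, and of the NNRD the Introduction says "This holds information on all babies admitted for NHS neonatal care". The document does not support that reading:
- The EPR items used are not listed, so a usable severity marker is likely but not shown.
- The Abstract describes the NNRD as formed from deidentified data, and nothing shows that it can be joined to a parent's survey.
- The planned 3-month NNRD baseline serves data completeness, whereas the survey baseline is a separate 6-week evaluation with no stated link to a baby.

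Whole-unit case mix would not fill the gap. In the first roll-out weeks respondents come from SCBU, while the unit's case mix still includes HDU and ICU.

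Nor does the protocol say that severity cannot be measured. It says only that it is not being measured.

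**Conclusion.** The point holds for level of care. Unit area is known for each recruited parent, is tied to calendar time by the roll-out, and is not named for adjustment or stratification; nor is change in condition. The small-pilot reason does not cover area.

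Distortion of the run-chart trend follows from the design if satisfaction is related to severity, as the authors themselves expect. Bias in the period comparison is possible, but its size and sign are unknown. The range of 0.03 to 0.21 SD rests wholly on assumed differences of 0.3 to 0.7 SD and 10 to 30 points. This is a worthwhile and inexpensive correction to a pilot, and it does not invalidate the design.

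**What to change.** - Record the baby's unit area on the survey date on every PEC survey. Do the same for baseline service-evaluation surveys where area is already recorded or can still be added.
- Stratify the run charts by area.
- Compare the two periods within area, or adjusted for area together with gestational age and length of stay. The demographic form is described for recruited parents only, so check whether these two variables exist for baseline respondents.
- For recruited parents, add a simple condition marker from the daily EPR if one is available and the approval covers that use.
- Revise the Discussion sentence so that the unmeasured factors are parental anxiety, depressive symptoms and residual severity. State the area mix of the baseline surveys, or say that it is unknown.

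The cost is one extra field per survey and a line of analysis text, with no new participants. The drawbacks are smaller strata, and incomplete adjustment if baseline surveys carry no area. In that case the period comparison should be reported with that caveat, and the area-stratified run charts for the intervention period would still be usable.
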